## Study Objectives

The primary objective of this study is to assess the feasibility of delivering a multimodal surgical prehabilitation service to surgical oncology patients. The secondary objectives are to explore the effectiveness of the program using clinical, physical, and patient-reported outcome measures. The specific research questions guiding this study design are listed in **Box 1**.

**BOX 1**. Study Research Questions.Feasibility Research Questions:RQ1a: How many referrals for prehabilitation will be received and what are the identified indications for prehabilitation?RQ1b: Does a surgeon’s bedside assessment of frailty (as indicated by referral and reason for referral) correspond with established frailty indices?RQ1c: What percentage of referred patients participate in prehabilitation?RQ1d: What are the demographic and medical characteristics of patients who are referred to for prehabilitation?RQ1e: What factors contribute to participants choosing either FBP or HBP?RQ1f: What is the ‘prehabilitation window’ for participants (i.e., time from treatment decision to surgery)?RQ1g: What is the adherence rate to the multimodal components defined by the prehabilitation protocols?RQ1h: Is prehabilitation safe within a clinical model of care (i.e., number and nature of adverse events)?RQ1i: What are the barriers and facilitators to prehabilitation?RQ1j: What are the various costs and potential cost savings associated prehabilitation?Exploratory Effectiveness Research Questions:RQ2a: What changes in clinically relevant outcomes do participants experience by the week prior to surgery and up to 90 days after surgery?RQ2b: Compared to usual care, what effect does prehabilitation have on peri- and postoperative outcomes (up to 90 days after surgery)?(RQ, Research Question)

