## Methods

### Design

This is a pragmatic, preference-based, non-blinded, non-randomized trial to assess the feasibility and estimates of effectiveness of a clinically integrated, multimodal prehabilitation program for frail surgical oncology patients in an urban academic health center in Toronto, Ontario, Canada. Participant flow throughout the study is presented in **Figure 1**. The initial study protocol and subsequent amendments related to the COVID-19 pandemic have been approved by the University Health Network research ethics board.

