#### Exercise

Each participant’s exercise prescription is developed and delivered by a kinesiologist and individualized to the results and observations obtained during the baseline assessment. Participants in both groups receive a moderate intensity aerobic and resistance training prescription to be completed 3–5 times per week for 60 min per session. Exercises specific to the anticipated locoregional impairments associated with the pending surgery are also prescribed for FBP and HBP participants to be completed independently. Participants in FBP are encouraged to attend two facility-based sessions per week where the aerobic training includes HIIT using the 10 × 1 protocol (51), and on such days, resistance training using the facility’s equipment is commenced after a 10 min rest period. All home- or community-based exercise sessions are supported with the provision of a stability ball, resistance bands, and a manual free of charge, and are intended to be completed independently (*i.e.*, unsupervised). Prior to initiating the exercise program, all exercises are instructed and demonstrated in the prehabilitation program facility where participants have an opportunity to practice and receive feedback/corrections or alternate exercises. The kinesiologist communicates weekly with participants by telephone to support program compliance, record adherence, appropriate progression, and to address any barriers to exercise that may prevent participation. Details of the aerobic and resistance training programs, as well as the locoregional impairment-based exercises are provided in **Tables 1** and **2**, respectively.

**Table 1 T1:** Exercise-based Total Body Prehabilitation.

	Home-based prehabilitation (HBP)	Facility-based prehabilitation (FBP)
Frequency	3–5 sessions per week (plus additional sessions for locoregional exercises as indicated)	
Intensity—Aerobic	MICT at 40–70% HRR or an RPE of 4–7/10	Home-based sessions are as per HBP. Facility-based sessions (twice weekly) employ the 10 × 1 HIIT protocol (10 cycles of exercise and recovery intervals, each interval is 1 min). During the first week, exercise intervals are 70–80% VO_2peak_ in session 1 and 75–85% VO_2peak_ in session 2 with recovery interval at a target an intensity of ≤50% VO_2peak_. In the second week and up to date of surgery, the exercise interval intensity target is set to 85–95% VO_2peak_.
Intensity—Resistance	2–3 sets of 8–12 repetitions at approximately 12–15 repetition maximum	

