### Study Outcomes

Participant data to assess feasibility and derive estimates of effect are collected from the participants’ referrals, at the baseline assessment, within 1 week prior to surgery, and at 30 and 90 days postoperatively.

The total number of referrals and the rate at which they are received (per month) will be reported. To characterize the patients referred to the program, the following are collected from all referral forms (including usual care participants and those who decline research): referring surgical service; reason for referral; frailty level (*via* the Clinical Frailty Scale (3), embedded into the referral); cancer type; indicated surgery; referring healthcare practitioner type (*i.e.* physician, surgeon, clinic nurse, *etc.*), and participant demographics (age, sex, and general geographic location). The enrolment rate will be calculated as [# of enrolled participants]/[# of referred participants]. The frequency and reasons for declining participation in the study, declining prehabilitation (*i.e.*, usual care participants), and drop-out will be reported and compared using descriptive statistics of demographic and referral data.

Given the importance of scheduling and timing for prehabilitation relative to the date of surgery, several relevant time periods will be reported. The time from program referral to the date of surgery will be reported and is referred to as the ‘prehabilitation window’. We will also report the total preoperative period (time between consent for surgery and date of surgery) and prehabilitation duration (time from baseline assessment to surgery).

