Reporting of the exercise prescription parameters and adherence to the programming will follow the Consensus on Exercise Reporting Template (62). Adherence to home and facility-based exercise sessions are recorded *via* attendance and standardized logbooks capturing training activity completed by the research coordinator. Adherence to stress management, nutrition plan, protein consumption, and utilization of smoking cessation tools (as required) is recorded weekly using a logbook within the participant manuals. Healthy eating practices advised by the dietitian are also assessed by a 3-day diet record in the week prior to surgery. Safety or adverse events related to prehabilitation are discussed during weekly communication between the participants and the research coordinator. Reporting and grading of adverse events will follow the Common Terminology Criteria for Adverse Events version 5.0 (63).

Estimates of program effectiveness are derived from a combination of patient-reported and functional performance measures, as well as clinical information from the medical record at each of the study timepoints. Aerobic functional capacity is measured using the Six-Minute Walk Test (6MWT) (64) and musculoskeletal functional capacity is assessed *via* grip strength using an isometric dynamometry (Jamar, Sammons Preston, Bolingbrook, IL, U.S.A.) according to established protocols (44). Body mass (kilograms) and height (meters) are measured using standardized procedures and are used to calculate body mass index (BMI, kg/m^2^). Body fat percentage, fat and fat free mass, impedance, resistance, and phase angle are recorded are measured *via* bioelectrical impedance analysis (mBCA 514, Seca, Hamburg, Germany) (65). HRQOL is measured using the 12-item Short Form Health Survey (SF-12) (66, 67) and the EuroQol 5 Dimensions 5 Levels (EQ5D-5L) (68) The Patient Health Questionnaire (PHQ-9) is used to assess depression (69). The EFS, PSS, and GLTEQ are also re-administered at each follow-up timepoint. Postoperative length of stay in number of days (including any readmissions) is recorded from the medical record. Complications, including mortality, are reported according to the Clavien-Dindo classification (70). All health events that require readmission will also be documented. Complication and health event data are extracted from the medical record at the 30^th^ and 90^th^ postoperative day for each participant.

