### Analytic Plan

The analytic plan is described for prehabilitation implementation feasibility outcomes and exploratory analyses of prehabilitation effects. In line with comparative effectiveness research, presentation of confidence intervals will be emphasized for the purpose of accurately reflecting the actual data as well as directly addressing the uncertainty of the data. All quantitative analyses will be conducted in R (R Foundation for Statistical Computing, Vienna, Austria) and an alpha of.05 will be used.

Demographic and disease characteristics of all referred patients, as well as prehabilitation and usual care participants**’** will be summarized with appropriate parametric and non-parametric statistics. Reasons for ineligibility, declined participation in the study or intervention, as well as reasons for choosing FBP or HBP will be tallied. Group comparisons for referral information (surgical service, type of cancer, type of surgery, age, sex, and geographic location) will be assessed by one-way analysis of variance (ANOVA) for continuous and Chi-square test for categorical variables and described across FBP, HBP, usual care, and participants who decline participation. Baseline demographic and disease-related variables will be compared between study participants (FBP, HBP and usual care) ***via*** one-way ANOVA for continuous variables and Chi-square test for categorical variables.

Adherence to the interventions will be summarized dichotomously as meeting or not meeting the prescribed intervention components across each domain (exercise, nutrition, psychology, and smoking cessation). Reasons for deviations will be thematically categorized and summarized by frequency and percentage. Retention rates will be calculated as a total percentage of dropouts at the presurgical time point to the total participants enrolled for FBP and HBP. Reasons for dropout will be summarized using frequencies and percentage for each prehabilitation arm. Reported safety or adverse events will be summarized using frequencies and percentage for each group.

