### Protocol Adaptations in Response to the COVID-19 Pandemic

COVID-19 containment measures have reduced elective surgery volumes around the world. Reduced surgical capacity has led to longer wait times for elective procedures and patients are experiencing declining physiological and psychosocial health in the unsettling context of social distancing, community service closures, and economic hardship. This loss in health is likely to be most profound for older patients and those with complex medical needs. Consequently, the extended waiting time is likely to negatively impact disease progression and surgical tolerance that may lead to higher rates of adverse surgical outcomes, ultimately compounding COVID-19-related health system strain. Given that prehabilitation may play an important role in mitigating the deterioration of health and well-being during extended surgical wait times, this study implemented several amendments to accommodate pandemic-related restrictions and barriers to healthcare in an attempt to maintain the opportunity for prehabilitation participation for planned but unscheduled, or delayed, cancer surgery. A summary of the amendments approved by the institutional ethics board is provided in **Box 2**.

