**BOX 2**. COVID-19 Pandemic-Related Study Accommodations.1. Extension of enrolment period by at least 6 months to accommodate pauses in research and to initiate contactless study protocols2. Accept form-fillable PDF referrals by email from clinicians (*versus* referrals by fax)3. Informed consent is obtained verbally, by phone, with informed consent documentation emailed to participants to be completed and returned at their next hospital visit (*e.g.*, date of surgery, post-operative clinic visit)4. All interactions between participants and study staff, including the baseline assessment, are completed by telephone or web conferencing (Microsoft Teams, Redmond, Washington, USA)5. Exercise equipment, manuals, and protein supplementation are mailed to participants6. All exercise sessions are intended to be conducted at-home and employ the same exercise parameters for HBP described in **Table 1**. Additional emphasis on strategies to maintain social distancing is provided for those who are engaging in outdoor exercise.7. Study outcomes requiring an in-person assessment (*e.g.*, 6MWT, body composition, grip strength) are omitted during in-person research restrictions, and only data derived from questionnaires and the electronic medical record are collected for exploratory analyses of effectiveness

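### Adverse events are summarised only as counts and percentages, with no link to time on programme, which varies by patient and probably by period

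*Protocol article*

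**What the plan says.** The safety summary is one sentence in the Analytic Plan: "Reported safety or adverse events will be summarized using frequencies and percentage for each group". It gives no time denominator, no confidence interval and no split by period.

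Other sections describe the exposure:

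- Study Outcomes defines prehabilitation duration as the time from the baseline assessment to surgery and says it will be reported. There is no fixed programme length. Table 1 likewise ties training to the operation date: "In the second week and up to date of surgery, the exercise interval intensity target is set to 85–95% VO_2peak".
- Events are elicited at regular contacts: "Safety or adverse events related to prehabilitation are discussed during weekly communication between the participants and the research coordinator".
- The section on pandemic adaptations says: "Reduced surgical capacity has led to longer wait times for elective procedures". It keeps the programme open to patients whose surgery was planned but had no date, or was postponed.
- Box 2, item 6, on the same period: "All exercise sessions are intended to be conducted at-home and employ the same exercise parameters for HBP".
- Streams are chosen, not assigned. The Design section begins: "This is a pragmatic, preference-based, non-blinded, non-randomized trial".

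RQ1h in Box 1 asks whether the programme is safe in clinical care, and means by this how many adverse events occur and of what kind.

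**The concern.** A percentage of patients with an event depends on two things: how often events occur per week, and how many weeks each patient was observed. Here the second varies from patient to patient with the surgical wait. The documents also give a reason to expect it to vary by calendar period, and delivery mode is tied to period because no facility exercise took place under the restrictions.

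Safety is one of the feasibility questions, and feasibility is the primary objective. Readers planning a service will want to know the risk per week of programme, because their own waiting times will differ from this hospital's. A percentage without time at risk cannot be carried over to a service with a different wait. If one stream or period had longer exposure, its percentage would be higher at the same weekly rate. If the group with the higher rate had the shorter exposure, the percentages could look alike.

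The article treats other events differently. The Analytic Plan specifies incidence rate ratios and rate differences for postoperative complications and readmissions at 30 and 90 days, where observation time is nearly the same for everyone. It also says confidence intervals will be emphasised. Programme adverse events, where observation time does vary, get neither.

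**Working it through.** **The plan's own figure.** There is none to reproduce. The documents give no adverse-event rate, no expected programme length and no precision target for safety.

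**Inputs from the documents.** 150 anticipated referrals, of whom one third are expected to decline the intervention (Sample Size). That leaves at most 150 − 150/3 = 100 prehabilitation participants.

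**Inputs that are assumptions.** A constant weekly event rate *r* of 1 to 10 per 100 participant-weeks; mean time on programme *t* of 4, 6, 8 or 12 weeks; 50 patients per group.

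**Step 1: crude percentage.** The share with at least one event is 1 − exp(−*r* × *t*). At *r* = 0.02:

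- 4 weeks: 1 − exp(−0.08) = 7.7%
- 12 weeks: 1 − exp(−0.24) = 21.3%

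Over the assumed range:

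| Events per 100 participant-weeks | 4 wk | 6 wk | 8 wk | 12 wk | Ratio 6:4 | Ratio 8:4 | Ratio 12:4 |
|---|---|---|---|---|---|---|---|
| 1 | 3.9% | 5.8% | 7.7% | 11.3% | 1.49 | 1.96 | 2.88 |
| 2 | 7.7% | 11.3% | 14.8% | 21.3% | 1.47 | 1.92 | 2.78 |
| 5 | 18.1% | 25.9% | 33.0% | 45.1% | 1.43 | 1.82 | 2.49 |
| 10 | 33.0% | 45.1% | 55.1% | 69.9% | 1.37 | 1.67 | 2.12 |

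Every ratio would be 1.00 if durations were equal. The ratios above 1 come from duration alone.

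**Step 2: masking.** Suppose one stream has 4 events per 100 participant-weeks over 4 weeks and the other 2 per 100 over 8 weeks. Both give 1 − exp(−0.16) = 14.8%. A twofold difference in weekly rate disappears.

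**Step 3: rate with time at risk.** Expected events are *n* × *r* × *t*. With *n* = 50 and *r* = 0.02:

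- 4 weeks: 4 events in 200 participant-weeks = 2.0 per 100
- 12 weeks: 12 events in 600 participant-weeks = 2.0 per 100

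The rate is the same whatever the duration.

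**Step 4: precision.** With 4 events in 200 participant-weeks, treated as independent, the exact Poisson 95% limits on the count are 1.09 and 10.24. Dividing by 2 gives about 0.5 to 5.1 per 100 participant-weeks. The estimate will be imprecise.

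**The case against.** The strongest reply is that the plan answers the question it asks. RQ1h wants the number and kind of events, and counts with percentages, graded by CTCAE version 5.0, supply that. No between-stream safety test is planned. Duration will be reported in its own right, so a reader will see exposure somewhere in the results. An article may also leave a rate table to a fuller document that is not shown.

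Much of this stands, and it is why the point is minor. It does not remove the point. The summary measure is stated, and a better one is available from data the trial already reports. Separate summaries of duration and of events do not link the two.

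A reader might go further and infer that FBP and HBP differ in time on programme, so that HBP will look less safe than it is. The documents do not support that. No section says durations differ by stream, and no figure is given for the longer waits. The Abstract describes a separate virtual program, and Box 2 says only that it uses the HBP exercise parameters; nothing says its participants will be pooled with HBP in the safety table. The link from longer waits to a particular stream is an inference.

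The arithmetic also has limits. The rates and weeks are assumptions, and 12 against 4 weeks is a wide contrast; 6 against 4 gives ratios of only 1.37 to 1.49. If events cluster in the first weeks, the distortion shrinks. Weekly elicitation is not a separate bias: it is part of how longer exposure yields more reports.

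**Conclusion.** The point holds as a minor weakness in the choice of summary. Time on programme varies by patient and is expected to be longer in the pandemic period, yet adverse events are to be reported with no reference to it. If durations differ between streams or periods, crude percentages may mislead in either direction. Under a constant rate the apparent ratio is about 1.4 to 1.5 for 6 against 4 weeks and 2.1 to 2.9 for 12 against 4, and there is no distortion if durations are equal.

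These sizes rest on assumed rates and durations, and on events arising evenly over time. It cannot be concluded that any stream will look less safe than it is, because the documents do not show a difference in exposure by stream. Nor would a rate make the streams comparable: patients choose their stream, and only FBP includes facility-based interval training.

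**What to change.** Keep the planned counts and percentages and add to the Analytic Plan:

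- Events per 100 participant-weeks, counting time from the baseline assessment to surgery or dropout, by stream.
- Virtual-period participants shown separately from in-person HBP. A full stream-by-period table is not useful, since there is no facility exercise under the restrictions and the other cells would be sparse.
- 95% confidence intervals that allow for repeat events in one patient: for example a patient-level bootstrap, or an exact Poisson interval on first events with time censored at the first event. A plain Poisson interval on all events would tend to be too narrow.
- Any per-session rate limited to supervised facility sessions. Home sessions are unsupervised, the article itself notes that self-report may be biased, and Table 1 lets a session be divided, so their count is not a comparable denominator.

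The cost is a sentence or two and one table. Duration to surgery is already a reported outcome. The date of dropout is also needed; the article does not say it is recorded, but the weekly contacts should supply it. The downside is wide intervals, because events will be few, and the comparison between streams stays descriptive.

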**Methods:**

This is a pilot pragmatic clinical trial conducted in a large academic hospital in Toronto, Ontario, Canada to assess feasibility of clinical implementation and derive estimates of effectiveness. Feasibility data include program referral rates, enrolment and attrition, intervention adherence and safety, participant satisfaction, and barriers and facilitators to programming. The study aims to receive 150 eligible referrals for adult, English-speaking, preoperative oncology patients with an identified indication for prehabilitation (*e.g*., frailty, deconditioning, malnutrition, psychological distress). Study participants undergo a baseline assessment and shared-decision making regarding the intervention setting: either facility-based prehabilitation or home-based prehabilitation. In both scenarios, participants receive an individualized exercise prescription, stress-reduction psychological support, nutrition counseling, and protein supplementation, and if appropriate, smoking cessation program referrals. Secondary objectives include estimating intervention effects at the week prior to surgery and 30 and 90 days postoperatively. Outcomes include surgical complications, postoperative length of stay, mortality, hospital readmissions, physical fitness, psychological well-being, and quality of life. Data from participants who decline the intervention but consent for research-related access to health records will serve as comparators. The COVID-19 pandemic required the introduction of a ‘virtual program’ using only telephone or internet-based communication for screening, assessments, or intervention was introduced.

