### Sample Size

A period of trial enrolment, rather than target sample size, was selected to inform expected rates of referral for a clinical service. The trial anticipates receiving 150 referrals for prehabilitation over 12 months. We estimate that one third of all referred patients will decline the intervention but will consent to making their hospital records related to their pending cancer surgery available for research (hereafter referred to as ‘usual care’ participants).

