To provide an estimate of effect of HBP and FBP, point estimates and 95% confidence intervals will be calculated for changes in physical fitness, patient-reported outcomes from baseline to the 90-day time point using linear mixed effect models. Estimated mean hospital length of stay for HBP, FBP, and usual care, as well as between-group differences, will also be conducted using a linear mixed effect model. Incidence rate ratios and estimating rate differences for postoperative complication, readmission, and morbidity for prehabilitation in reference to usual care at 30 and 90 days after surgery will be made using Poisson regression. Tukey HSD will be used to adjust for multiple comparisons. In the presence of outliers, bootstrapping regression coefficient methodology will be done to obtain valid confidence intervals.

Semi-structured interviews regarding participant satisfaction as well as facilitators and barriers with the intervention will be transcribed verbatim and undergo qualitative content analysis. Initial transcript sample readings will be independently done by two researchers. Preliminary themes will be noted, and differences will be resolved, and duplications will be eliminated. Themes and content will be analyzed descriptively. Coding, linking, and retrieving the qualitative data will be conducted using NVivo software (QSR International, Melbourne, AUS).

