There are several strengths of this study. First, the pragmatic, preference-based trial design with robust implementation feasibility outcomes and measures of effectiveness will add important information to the prehabilitation literature that is currently lacking in these areas. Second, the prehabilitation interventions are multimodal and comprehensive within each modality intended to replicate gold-standard practice. Moreover, the interventionists represent the appropriate scopes of practice and clinical professions most qualified and likely to be involved in an interprofessional, multimodal clinical prehabilitation service. Third, by including a usual care arm, we have a control comparator for effect size estimates. Fourth, we have amended our research protocol to respond to the evolving context of the COVID-19 pandemic by pivoting towards contactless study participation. This study also has noteworthy limitations. The sample size will likely lack the statistical power to draw precise conclusions about the effect of the interventions. Similarly, in the absence of an RCT design, our interpretations of comparisons with usual care participants may be limited due to group differences in those who do versus those who do not wish to engage in prehabilitation. Interpretation of the findings will also be limited to the types of surgeries for which prehabilitation precedes which may be skewed to the physicians and healthcare teams who are in favour of prehabilitation and refer patients to our study. This highlights potential sampling and participation biases as participants will more likely be referred and participate in our program if their healthcare team implicitly endorses it by virtue of discussing it and making a referral. Similarly, the breadth of cancer surgeries and their extreme heterogeneity within a relatively small sample will limit sub-group analyses related to estimates of intervention effect.

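### Within-arm change in fitness and patient-reported outcomes is labelled an effect estimate, although usual care supplies no comparator data for these outcomes

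*Protocol article*

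**What the plan says.** The Analytic Plan opens its effectiveness paragraph with "To provide an estimate of effect of HBP and FBP, point estimates and 95% confidence intervals will be calculated for changes in physical fitness" and continues with "patient-reported outcomes from baseline to the 90-day time point using linear mixed effect models". Usual care is named later in that paragraph, for length of stay and for the Poisson models of complications, readmission and morbidity.

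Study Outcomes treats the questionnaires and physical tests as evidence of effectiveness: "Estimates of program effectiveness are derived from a combination of patient-reported and functional performance measures", together with medical-record data.

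Usual care is defined by its data source. The Sample Size section expects that "one third of all referred patients will decline the intervention but will consent to making their hospital records" available. The Abstract says that "participants who decline the intervention but consent for research-related access to health records will serve as comparators". Study Outcomes adds one further source, the referral form, which is collected for every referred patient, "including usual care participants and those who decline research".

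The Discussion lists as a strength that "by including a usual care arm, we have a control comparator for effect size estimates", with no restriction by outcome.

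**The concern.** A change score in treated patients equals a treatment effect only if the score would have stayed flat without treatment. The article gives reasons to doubt that. The Introduction says quality-of-life problems are common after cancer surgery. The COVID-19 section says patients on longer waiting lists are losing physical and psychosocial health. On that account, no change at all could be a benefit. Retesting and recovery from earlier treatment could push scores the other way. Baseline to day 90 also spans the operation itself.

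At stake is what the trial may conclude. Under the present label, a day-90 decline caused by surgery reads as harm from the programme, and an improvement due to recovery reads as benefit. The unrestricted comparator sentence suggests that such influences have been controlled for these outcomes. They have not.

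**Working it through.** **1. Which outcomes have usual-care data**

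| Outcome | Source | Planned in usual care? | Usual-care contrast in the Analytic Plan? |
|---|---|---|---|
| Length of stay | Medical record | Yes | Yes |
| Complications (including mortality), readmission | Medical record | Yes | Yes |
| 6MWT, grip, body composition | In-person test | No section plans it | No |
| SF-12, EQ5D-5L, PHQ-9, PSS, GLTEQ | Questionnaire | No section plans it | No |

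Referral-form items (service, reason for referral, Clinical Frailty Scale, cancer, surgery, demographics) describe usual care patients at entry. They include no follow-up fitness or questionnaire score.

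**2. The label against the research questions**

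Box 1 keeps two questions apart. RQ2a asks what *changes* participants experience up to 90 days after surgery. RQ2b asks what *effect* prehabilitation has compared with usual care. The Analytic Plan computes the RQ2a quantity for fitness and patient-reported outcomes, but introduces it as an effect.

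**3. The presurgical time point**

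The Abstract lists estimating intervention effects in the week before surgery among the secondary objectives. Length of stay, postoperative complications and readmissions do not yet exist then. No planned usual-care contrast can supply an effect estimate at that visit, so only within-arm change is available.

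**4. What the interval covers (illustration only)**

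The article states no effect size, SD or power for these outcomes, so there is no figure of its own to reproduce. The group sizes below are assumptions derived from the Sample Size section:

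- Expected usual care: 150 / 3 = 50.
- FBP and HBP together: at most 150 − 50 = 100, if every other referral enrols.
- An even FBP/HBP split would give 50 per arm.

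The 95% half-width of a mean change, in units of the SD of change, is 1.96/√n:

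- n=100: 1.96/10 = 0.196
- n=50: 1.96/7.071 = 0.277

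Had usual care supplied the same scores, the half-width for a difference in change would be 1.96 × √(1/n₁ + 1/n₂):

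- 100 v 50: 0.339
- 50 v 50: 0.392

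The uncontrolled interval is thus narrower than a controlled one would be, because it leaves out what an untreated group would have shown.

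Suppose scores would shift by b SD of change without the programme. The nominal 95% interval then covers the true programme effect with probability Φ(1.96 − b√n) − Φ(−1.96 − b√n). The sign of b does not matter.

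- b=0.2, n=50: b√n = 1.414; Φ(0.546) − Φ(−3.374) = 0.707
- b=0.2, n=100: b√n = 2.0; Φ(−0.04) − Φ(−3.96) = 0.484

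| Background shift b | Coverage, n=50 | Coverage, n=100 |
|---|---|---|
| 0.1 | 89% | 83% |
| 0.2 | 71% | 48% |
| 0.3 | 44% | 15% |
| 0.5 | 6% | 0.1% |

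A larger sample makes coverage worse, because the interval tightens around the wrong quantity.

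**The case against.** The case for leaving the text alone is reasonable. Feasibility is the primary objective, and effectiveness is only to be explored. The design is openly non-randomized, and the analyses are called exploratory. The Abstract and Sample Size section say plainly that usual care means access to records, and the Analytic Plan uses the word *changes* within the sentence at issue. A careful reader can work out which outcomes have a comparator. No computed quantity is wrong.

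Most of that is true, and it keeps this a point about labels and claims. It does not dispose of it. The limitations paragraph admits low power and possible group differences in comparisons with usual care. That caveat presupposes a comparison, and for these outcomes there is none.

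Some stronger readings are tempting but not supported:

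- *The bias can be sized as regression to the mean.* A reader might suppose that referred patients are the lowest third on a measure with test-retest correlation 0.8, giving 0.2 × 1.091 = 0.218 SD of spurious gain. That assumes selection on the baseline score. Here referral rests on clinical judgement and comes before the baseline assessment, and no test threshold governs entry. With a stable trait and independent errors, selection on an earlier score gives no expected change after baseline. Nor would such a shift always produce a false positive: for the lowest half and correlation 0.9 it is 0.080 SD against a half-width of 0.086 at n=100, so the interval includes zero.
- *The trial has no comparator at all.* Usual care is a comparator, though a self-selected one, for length of stay, complications and readmission.
- *FBP against HBP fills the gap.* Both arms are treated and chosen by preference, so neither shows what happens without the programme.
- *The figures will be used to size a later trial.* The article states no such plan.

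**Conclusion.** The point holds as one of labelling and claim. For physical fitness and patient-reported outcomes, the plan yields uncontrolled change within each prehabilitation arm. The Analytic Plan calls that an estimate of effect, and the Discussion claims a comparator without excluding these outcomes. The Abstract's secondary objective and the Conclusion's promise of effect estimates for two models carry the same wording.

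The size of the bias is unknown, and it could run in either direction. The coverage figures show only how quickly a nominal 95% interval fails when an unmeasured shift is present. They rest on assumed shifts, assumed group sizes and a simple normal mean, and they do not predict this trial's results. The conclusion does not depend on them; it follows from the definition of usual care and the list of outcomes. The primary feasibility objective and the record-derived comparisons are unaffected by this point.

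**What to change.** - **Analytic Plan:** describe the fitness and patient-reported results as within-arm change with 95% confidence intervals, matching RQ2a. Reserve effect language for record-derived outcomes that usual care also supplies: length of stay, complications including mortality, and readmission.
- **Discussion, strengths:** limit the comparator statement to those record-derived outcomes.
- **Discussion, limitations:** add that fitness and patient-reported outcomes have no usual-care comparator, so their change also reflects surgery, waiting time, recovery and retesting.
- **Abstract and Conclusion:** align the effect wording, including the reference to effects in the week before surgery.

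The cost is a less favourable claim. No data collection, model or sample size changes.
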